**Fig. 2 Fig2:**
[figure not shown]
Graphical model of the cohort study [39]. (**A**) Structured questionnaires. (**B**) Structural, epidemiological, demographic, and economic quantitative data. (**C**) Continuous individual qualitative interviews with selected patients and relatives (and staff of the day hospice) throughout the survey phase

### Recruitment

Identification of appropriate patients and their primary caregiver will be performed in the day hospice by trained staff under the direction of the nursing director, a palliative care specialist (MSc) with an academic degree in applied health services research, or by proxy by study center personnel. The control cohort will be recruited – after appropriate study training – by the physicians of the oncology–palliative care network of Lower Bavaria at the respective locations. The experts for the qualitative interviews are involved by the authors or study leadership team.

### Expected sample size

This study aims to collect real world data and is explorative and observational in character. The sample size is therefore based on feasibility and the case load of the day hospice. The recruitment period for the cohort study will be 18 months. During this period, a consecutive sample of patients meeting the inclusion and exclusion criteria will be included. A caseload of 80 patients with life-limiting illness and an equally large number of the respective relatives in the catchment area of the day hospice (intervention group day hospice) is expected. Likewise, 80 patients with life-limiting illness and an equally large number of the respective relatives outside the catchment area of the day hospice (control group non-day hospice) is expected. Failures are expected in the group of relatives, among other things, due to lack of motivation to participate, patient’s wish, or fundamental lack of relatives. A sample size of 80 patients per group is deemed sufficient according to the literature to estimate the effect of our exploratory endpoints [36, 37].

### Inclusion and exclusion criteria

*Specific admission criteria apply for day hospice visits:*

Presence of an incurable disease in a very advanced or terminal stage.Home care is ensured so that the patient is most likely to return home after visiting the day hospice, and a transfer directly from the day hospice to a full inpatient facility is not necessary.The journey to the day hospice is possible in a seated position (e.g., by a transport service or relatives).No presence of symptoms that potentially endanger the patients themselves, other guests, or day hospice staff members.Ability to fit into the day hospice community and participate in the services/activities offered.No complete bedriddenness.Age > 18 years.

In principle, admission to the day hospice is always possible regardless of study participation.

*In the present study, the following additional inclusion and exclusion criteria are defined*:

The key inclusion criteria are:

Care within the oncology–palliative care network Lower Bavaria.Presence of severe and life-limiting hematologic/oncologic disease.Defined admission criteria for day hospice visit met.

Key exclusion criteria are:

The absence of care within the oncology–palliative care network Lower Bavaria.Inability to answer the questionnaires.Defined admission criteria for the visit in the day hospice not met.

*In principle, the inclusion and exclusion criteria can still be modified according to the results of Stages 1 and 2.*

### Data collection, data storage, and data security

To create a protected atmosphere for the participants of the day hospice, the interviews will take place in a separate room in the day hospice. The supervising nurse can always be called, if necessary. A study nurse will also available on site during the interview for technical and organizational questions. Interviews for relatives and experts will take place at the day hospice or participants’ preferred location. The relatives will not be interviewed in the presence of the residents. The data obtained from the interviews will be documented pseudonymously.

All personal data will be handled in accordance with the applicable General Data Protection Regulation (DSGVO).

The medical, epidemiological, and demographic data of the guests of the day hospice are collected via the digital patient file (software system PalliDoc®) and recorded pseudonymously in a central database (eCRF). The questionnaires will be answered in writing by the patients or their relatives, marked pseudonymously, and collected in a sealed box. Within the framework of the cooperation between the oncology–palliative care network Landshut and the University Hospital Regensburg (Clinic and Polyclinic for Internal Medicine III, Center for Palliative Medicine), the analog study documents (including consent forms and questionnaires) will be stored in the archive of the cooperating VK&K Studien GbR. This is a lockable, fire, and waterproof room, to which only trained and documented study center staff have access.

The implementation and programming of the GCP- and DSGVO-compliant database are performed by a data manager from the Center for Clinical Trials Regensburg using the REDCap (Research Electronic Data Capture) system [38] and are hosted at the computer center of the University of Regensburg. REDCap is a browser-based database management system for clinical trials that can perform all essential data management functions (data security, entry, and validation) in a consistent, intuitive, and auditable electronic environment. Validity and consistency checks are programmed into the database. The database will be entered pseudonymously by study nurses on password-protected computers, which are located in lockable rooms of VK&K Studien GbR and are only accessible to their staff members. The Center for Clinical Studies Regensburg is responsible for query management and quality assurance. If inconsistencies exist or corrections to the data are necessary, data queries will be created by the data manager and sent electronically. The data will then be corrected according to the answered and solved queries. After database closure, data are imported into a statistical analysis program and analyzed by a biometrician at the Center for Clinical Trials.

A (pseudonymized) data exchange exists between the institutions conducting the study. For the planned interviews, the study participants’ personal data will be transmitted to the external institute conducting the interviews (SINUS Markt- und Sozialforschung GmbH) or collected by this institute. The participants’ written informed consent must be obtained in advance. Conclusions about the participants can only be drawn by persons directly involved in the study.

### Statistical analysis of quantitative data

The frequency of missing values per variable will be reported. Missing values will not be imputed, unless the handling of missing and ambiguous values will be specified in the manual of the selected measurement instrument. The questionnaires will be evaluated according to the associated manual and questionnaire scores defined in the manual are calculated. A descriptive analysis of the quantitative data will be performed. Depending on the scale level, absolute and relative frequencies will be reported for categorical variables and the mean, standard deviation, median, quartiles, and minimum and maximum for metric variables. Before-and-after comparisons between the survey of the measured variables before (T0, baseline) and after (T1 and T2) the intervention will be performed using appropriate statistical methods. Furthermore, comparisons will be made between the intervention (patients/relatives in the catchment area of the day hospice) and control (patients/relatives outside the catchment area of the day hospice) groups. In the abovementioned analyses, a family of endpoints comprising quality-of-life parameters, quality indicators, and structural and economic parameters is of interest. Due to the exploratory, observational study design, no corrections for multiple testing will be performed. If not defined otherwise, the significance level will be set to p_two−sided_ ≤0.05. Appropriate statistical programs will be used for all analyses, such as SPSS (version 29 or higher) or R (version 4.3.1 or higher). The reasons for departures will be documented.

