#### Stage 3: Evaluation phase (Evaluation)

The process test will be performed as follows:

Use of the quantitative indicators finally defined in Stage 2: structured questionnaires, quality indicators, and medical, epidemiological, demographic, and health economic data.Conduct an initial, baseline, quantitative effectiveness review on the potential benefits of the day hospice. For this purpose, a cohort study [35] with two comparison groups [A — “patients/relatives in the catchment area of the day hospice” (patients living in the catchment area of the day hospice: radius ≤ 25 km approach distance) vs. B — “patients/relatives outside the catchment area of the day hospice” (patients living outside the catchment area of the day hospice: radius > 25 km travel distance)] is planned [12]. The patients (and their relatives) in group A are also cared for in the day hospice, whereas, those in group B are not cared for in the day hospice, but medical care is provided in the same network structure (oncology–palliative care network Landshut, Lower Bavaria, Germany). The oncology–palliative care network Landshut includes several regional hematology–oncology outpatient clinics, an inpatient palliative medicine–oncology care unit, a SAPV, and an inpatient hospice. The network provides for the catchment area of the investigated day hospice and other regions without day hospice facilities to ensure comparability of the two cohorts based on the same oncology and palliative care structures.Due to the palliative disease situation of the participants with significantly limited life expectancy, quantitative data will be collected at the measurement time points T0 (baseline, after study inclusion), T1 (after 4 weeks), and T2 (after 8 weeks) (Fig. 2).Individual qualitative interviews will be conducted with the patients and their relatives on an ongoing basis during the evaluation phase in the same way as in Stage 1. Approximately 25–35 interviews are planned, with questions focusing on the perceived benefit from day hospice.

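### T0 is analysed as pre-intervention, but the stated rules tie it only to study inclusion and let current day-hospice guests enter group A with a baseline taken under exposure

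*Protocol article*

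**What the plan says.** All references are to the Protocol article.

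- **Statistical analysis of quantitative data.** The before-and-after comparison is between values "before (T0, baseline) and after (T1 and T2) the intervention". Intervention and control groups are also compared.
- **Stage 3: Evaluation phase, under Methods.** Data are collected at "T0 (baseline, after study inclusion), T1 (after 4 weeks), and T2 (after 8 weeks"). The only anchor for T0 is study inclusion. On exposure: "The patients (and their relatives) in group A are also cared for in the day hospice".
- **Recruitment.** For group A: "Identification of appropriate patients and their primary caregiver will be performed in the day hospice by trained staff". The control cohort is recruited "by the physicians of the oncology–palliative care network of Lower Bavaria at the respective locations".
- **Inclusion and exclusion criteria.** The key criterion on day-hospice use is "Defined admission criteria for day hospice visit met". The section also says: "In principle, admission to the day hospice is always possible regardless of study participation". No listed criterion requires a first visit or excludes people who already attend. The criteria may still be modified after Stages 1 and 2.
- **Expected sample size.** Over 18 months, "a consecutive sample of patients meeting the inclusion and exclusion criteria will be included"; 80 patients are expected per group.
- **Background and Stage 2.** The day hospice opened in April 2022, and a 6-month test phase there precedes Stage 3.

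**The concern.** The analysis needs a group A baseline that is free of the exposure. Enrolment is defined by rules that do not mention the start of exposure. Staff who followed them exactly could enrol someone who has attended for weeks or months and record the first questionnaire as the pre-intervention value.

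Two things are at stake. First, any benefit already reached by T0 is subtracted from group A's change. Follow-up is only 8 weeks, so a few weeks of earlier attendance can be a large part of the period in which change would be seen. Second, current guests are those who have survived and chosen to keep attending, so they may differ from new guests. The net direction of that selection cannot be read from the document.

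Later analysis cannot readily repair this if T0 was taken late and the date of first attendance was not collected.

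**Working it through.** **Step 1: does any visible rule place T0 before the first attendance?**

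| Element | What is fixed | Does it secure a pre-exposure T0? |
|---|---|---|
| Analysis label | T0 is before the intervention | States the intent only |
| T0 timing | After study inclusion | No: inclusion is not tied to first attendance |
| Place of identification, group A | In the day hospice | No: allows intake, but also current guests |
| Eligibility | Admission criteria met | No: a current guest can meet them too |
| Sampling | Consecutive among the eligible | No: not limited to new admissions |
| Setting | Open since April 2022, with a 6-month test phase before Stage 3 | No: guests can be present when recruitment starts |

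The label is the only element that points to a pre-exposure T0, and no operating rule enforces it.

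**Step 2: the plan's own figure.** The 80 per group rests on feasibility and case load. No effect size, SD or power is given, so there is nothing to reproduce, and this point does not change the figure.

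**Step 3: illustration of size.** Let d be the true standardised effect on the T0-to-follow-up contrast, p the share of group A already attending at T0, and f the share of the effect already present at T0 in those guests. The expected contrast is

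(1 − p)·d + p·(1 − f)·d = d·(1 − p·f).

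The document gives none of d, p or f; all are assumed. With d = 0.40 SD and f = 0.5:

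- 10 of 80 carry-overs, p = 0.125: 0.40 × (1 − 0.0625) = 0.375 SD
- 40 of 80 carry-overs, p = 0.5: 0.40 × (1 − 0.25) = 0.30 SD

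Varying f from 0.25 to 0.75 gives 0.3875 to 0.3625 SD at p = 0.125, and 0.35 to 0.25 SD at p = 0.5.

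**Step 4: what that means with 80 per group.** Under a normal approximation (SD 1, two-sided 5%, complete data), power = Φ(δ·√(80/2) − 1.960).

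| Contrast δ | δ·√40 − 1.960 | Power |
|---|---|---|
| 0.40 (no carry-over) | 0.570 | 71.6% |
| 0.375 | 0.412 | 66.0% |
| 0.30 | −0.063 | 47.5% |
| 0.25 | −0.379 | 35.2% |

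The smallest difference detectable with 80% power is (1.960 + 0.842) × √(2/80) = 0.443 SD. The assumed 0.40 SD is already below this without any carry-over, so that threshold does not measure the harm. The drop in the contrast and in power does.

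**The case against.** The strongest reply is that the document does not contradict itself. Inclusion, then T0, then first attendance satisfies both the timing rule and the analysis label, and the label shows that a pre-intervention T0 is intended. Identification in the day hospice fits screening at intake, where staff must check the admission criteria anyway. The sentence on admission regardless of study participation reads naturally as an assurance that care does not depend on consent. Fig. 2, the model of the cohort study, is not shown and may place T0 relative to admission. The listed criteria are only the key ones and can still change. The study is exploratory and makes no power claim.

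Much of this stands. A reader might infer that T0 is in fact taken on treatment; the document does not say so, only that nothing visible prevents it. A reader might also infer that group B has no starting point at all. That goes too far: group B must meet the same day-hospice admission criteria, and both groups take T0 after inclusion. What is unstated is the event that triggers inclusion in each group. Nor can bias in survival, hospitalisations or duration of home care be asserted, because Table 1 lists these only as potential parameters for quality indicators. Finally, a large share of carry-overs is not the obvious case. With 18 months of consecutive recruitment and patients of limited life expectancy, earlier guests would tend to cluster at the start.

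The reply does not remove the gap between the two rules. The article itself fixes both the anchor of T0 and its interpretation, and the first does not deliver the second. Being exploratory explains the absence of multiplicity control; it does not make a baseline under exposure a pre-intervention value.

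**Conclusion.** The point holds in a limited form. The visible sampling and timing rules admit current guests with a baseline taken under exposure, while the analysis treats that baseline as pre-intervention. If benefit has already arisen in those guests, group A's change and any between-group comparison of change are biased toward no effect.

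The size cannot be derived from the document. Under the stated assumptions (true effect 0.40 SD, half of it present at T0 in carry-over guests), the loss runs from small, 0.40 to 0.375 SD with 10 carry-overs among 80, to substantial, 0.40 to 0.30 SD with 40 among 80. With no carry-over guests, and T0 before first attendance for everyone else, there is no loss.

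It would be wrong to conclude that the comparison is invalid or that the study cannot detect a benefit; neither is established. Severity is moderate, because the study is exploratory and Fig. 2 and the full protocol are not visible. If either already places T0 before first attendance and restricts entry to new guests, the remaining task is to say so in the text.

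**What to change.** 1. State that Stage 3 group A consists of new admissions, with T0 completed at or before the first attendance day.
2. Record the date of first attendance for every group A patient.
3. Exclude guests already attending at the start of Stage 3 from the cohort comparison, or analyse them separately.
4. For group B, take T0 at a comparable point, such as the contact at which the day-hospice admission criteria are first confirmed as met, and record that date.

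These changes concern study enrolment and timing only; access to the day hospice is unaffected. They need one eligibility sentence, one timing rule and one date field per group, and the article already allows the criteria to be modified after Stages 1 and 2. The cost is that guests already attending when Stage 3 starts do not count toward the 80.

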### Dissemination and implementation

The research data and results of the different research sections will be published in recognized national or international journals and thus made accessible to a broad public. Additionally, the presentations of the research results will be planned at relevant scientific congresses.

## Discussion

To date, initial theoretical recommendations for day hospice implementation in Germany have been published [1, 13]. However, a review on daily clinical practice with systematic and structured implementation development in the sense of a complex intervention [16] and evaluation of the medical-nursing-care and economic effects are still missing. Therefore, for the future establishment of further day hospices in Germany, findings that go beyond theoretical recommendations or analogous conclusions from other countries and health care systems and have been obtained from the real-life situation are essential. Particularly, concrete advice on structural and interventional measures can be greatly beneficial. The planned study is intended to create an initial valid basis for the planning, practical establishment, and concrete implementation of new day hospices based on the real-life clinical care of a day hospice in Germany and/or to identify further necessary optimization processes. Additionally, initial data on the influence of day hospice care on, among other things, the quality of life, coping with illness, and care options of palliative patients and their relatives will be generated.

### Expected results

Specifically, our study results will provide the first real-world data on the feasibility and benefits of structurally developed and tested interventions and structures in a day hospice in Germany, which will include the followingInformation on structural requirements that is necessary for the establishment and daily operation of a day hospice and that is applicable, feasible, and reasonable in real-life clinical practice for all persons involved in the day hospice (patients, relatives, and caregivers).Development of a final interventional service catalog for day hospices that is tested under clinical conditions and can be implemented in real-life settings.Insights into the economic benefits of day hospices using health economic data.Development of an initial set of potential quality indicators for the (structural and outcome) assessment of day hospices.Insights into the potential benefits of day hospices for patients and relatives in the German healthcare system.

### Study risks

Stages 1 and 2 aimed to develop methods and implement the study investigation. The data collected will be primarily obtained from the literature and interviews with healthcare professionals, patients, their relatives, and experts. The main risk point here will be under-recruitment of interview participants, whether due to lack of interest, lack of time, reduced general health, or skepticism prior to study participation. Due to a good author network with palliative care professionals and experts as well as by a sufficiently large pool of potential patients and relatives from the day hospice, the risk of limited recruitment seems to be justifiably low. In Stage 3, recruitment of patients and their relatives in day hospice is planned for the cohort study. The patients from the oncology–palliative care network Lower Bavaria who are not cared for in the day hospice as well as their relatives are included as a comparison cohort. Particularly, in the comparison cohort, recruitment might therefore prove complicated, e.g., due to a lack of motivation among study participants. Through a total of five different recruitment sites, a sufficiently large number of potential inclusion candidates will be generated to also compensate for larger failures. Additionally, in Stages 1 and 2, an in-depth evaluation of the planned assessment tools and recruitment strategies will be conducted to early identify problematic issues and address them prior to the start of the actual cohort study.

## Conclusions

In our study protocol, we explained the implementation, realization, and benefits of a day hospice in Lower Bavaria of a quality-assured investigation on as well as the structures and interventions to be used. Our study results will be used to facilitate or enable the efficient establishment of day hospices under economic, health, and medical aspects. For the first time, the results of the interventions used and evaluated in real-world day hospice operations will be available. Our data will be used in developing further guidelines for the establishment and operation of day hospices under the aspects of benefit and financing. The present study protocol provides a detailed insight into the intended research objectives, thereby enabling other study groups to perform further investigations. The results of the present study could thus contribute to the further development of palliative care in Germany.

